#### 2.2.2. Exclusion Criteria

The exclusion criteria for the clinical anxiety group are (1) inability to read or understand the consent form; (2) significant difficulty using VR equipment (e.g., due to visual or vestibular impairment); (3) history of epilepsy, brain injury, or other neurological disorders; (4) severe physical illnesses (e.g., cancer, active tuberculosis, cardiovascular disease); (5) currently diagnosed with substance use disorder or alcohol use disorder (nicotine use will not be excluded); (6) presence of pacemakers or implanted metallic devices; (7) pregnancy or belonging to a legally or socially vulnerable population (e.g., institutionalized individuals or employees of the research facility); and (8) individuals who had previously completed a structured treatment protocol for anxiety within the past six months.

All exclusion criteria listed above apply to the healthy control group as well, with the addition of any previous or current psychiatric disorder.

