The primary objective of this study is to delineate neurobehavioral biomarkers associated with treatment response in individuals with anxiety-related disorders using a transdiagnostic approach. Specifically, the present study aims to delineate patterns of neural and behavioral markers that cut across diagnostic boundaries—including panic disorder, SAD, GAD, agoraphobia, and specific phobia—thereby capturing shared pathophysiological processes relevant to therapeutic responsiveness. Healthy controls are included as a reference group to distinguish disorder-related changes from normative variability. We hypothesized that multimodal integration of VR, EEG, 3D skeletal tracking, and neuroimaging data will enable a more mechanistic and predictive understanding of anxiety and its treatment response beyond categorical diagnoses.

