#### 2.2.1. Inclusion Criteria

The inclusion criteria for the clinical anxiety group are (1) adults aged between 19 and 60 years; (2) currently diagnosed with an anxiety disorder based on DSM-5 criteria, specifically including panic disorder, SAD, GAD, agoraphobia, or specific phobia, confirmed by a board-certified psychiatrist (individuals who have been previously treated for anxiety are not included); (3) ability to understand the purpose and procedures of the study and provide written informed consent, and (4) no history of major neurological disorders or psychotic illness.

The inclusion criteria for the healthy control group are (1) adults aged between 19 and 60 years; (2) no current or past psychiatric diagnoses and not currently using any psychotropic medication; and (3) ability to fully understand the purpose and procedures of the study and provide written informed consent.

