### 2.3. Recruitment Process and Screening for Enrollment

The clinical anxiety group will be recruited through outpatient psychiatric clinics at Samsung Kangbuk Hospital, where attending psychiatrists will identify individuals who meet the inclusion criteria. The healthy control group will be recruited via public announcements on institutional bulletin boards.

To confirm eligibility and psychiatric status, all participants will be evaluated by a board-certified psychiatrist using structured diagnostic interviews. The Structured Clinical Interview for DSM-5 Disorders will be used to verify diagnoses in the clinical anxiety group [27], while the Mini International Neuropsychiatric Interview (MINI) 5.0.0 will be administered to screen for comorbid conditions or to confirm the absence of psychiatric history in healthy controls [28].

All eligible participants will receive a detailed explanation of the study’s purpose, procedures, potential risks, and their rights. Written informed consent will be obtained before any assessments are conducted. Participation is entirely voluntary, and individuals may withdraw at any time without affecting their clinical care.

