### 3.2. Brain MRI Analysis

Preprocessing for MRI data will use standardized pipelines: fMRIPrep v24.0 for T1 and resting-state fMRI (anatomical segmentation, motion correction, spatial normalization, and smoothing at 6 mm full-width half maximum), and QSIPrep v0.21 for DWI (eddy-current correction, bias-field correction, and tensor fitting).

Structural MRI, diffusion-weighted imaging (DWI), and resting-state fMRI will be analyzed to comprehensively characterize brain structure, white matter integrity, and intrinsic functional organization associated with anxiety and treatment response. Structural MRI will yield cortical thickness and gray matter volume measures; DWI will provide white matter microstructural indices, including fractional anisotropy and mean diffusivity; and resting-state fMRI will be used to derive functional connectivity, amplitude of low-frequency fluctuations, and regional homogeneity as candidate neurobiological features for group comparisons and predictive modeling.

Group-level comparisons will be performed between (i) healthy controls and anxiety participants and (ii) responders and non-responders using general linear models with age and sex as covariates. Multiple comparisons will be adjusted using the false discovery rate. Significant neural indices will be further examined as candidate predictive features in multimodal modeling.

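### Controls must be free of any lifetime psychiatric disorder while patients may have comorbid depression, so the patient-control contrast, adjusted only for age and sex, cannot attribute a difference to anxiety

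*Protocol article*

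**What the plan says.** Section 2.2.1 requires controls to have "no current or past psychiatric diagnoses and not currently using any psychotropic medication". Section 2.2.2 repeats the bar as an exclusion: "All exclusion criteria listed above apply to the healthy control group as well, with the addition of any previous or current psychiatric disorder".

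For patients, the psychiatric restrictions beyond the index anxiety disorder are two. Section 2.2.1 asks for "no history of major neurological disorders or psychotic illness", and section 2.2.2 excludes a current substance or alcohol use disorder. Depressive disorders, current or past, are not mentioned. The restrictions on previous treatment concern anxiety only.

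The plan expects comorbidity. Under section 2.3 the MINI "will be administered to screen for comorbid conditions or to confirm the absence of psychiatric history in healthy controls". No exclusion, stratum or analysis step is tied to what it finds in patients.

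Section 3.2 compares controls with anxiety participants "using general linear models with age and sex as covariates" and takes significant indices forward as candidate predictive features. Section 3.4 lists age, sex, medication status and treatment type as possible covariates; comorbidity is not among them. The Introduction gives the purpose of the controls: "Healthy controls are included as a reference group to distinguish disorder-related changes from normative variability". The Abstract concludes with the identification of markers of anxiety and of treatment response.

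**The concern.** The two groups differ by design in more than anxiety. One is never-ill; the other has an anxiety disorder plus whatever depressive or other non-excluded disorders come with it. An imaging index altered in depression but not in anxiety would show up as a patient-control difference, and nothing in the stated model would reveal that. Such an index could be reported as a marker of anxiety and, under section 3.2, would be examined as a candidate feature.

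This is bias, not chance. False discovery rate control limits false positives under the null of no group difference. Here the groups truly differ, and only the attribution is wrong. A larger sample would make such an index more likely to be declared significant.

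**Working it through.** **The text, side by side**

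| | Controls | Patients |
|---|---|---|
| Psychotic illness | excluded | excluded (2.2.1) |
| Current substance or alcohol use disorder | excluded | excluded (2.2.2) |
| Depressive disorder, current or past | excluded | allowed |
| Other non-anxiety disorder | excluded | allowed |
| Covariates in the 3.2 model | age, sex | age, sex |

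The last three rows carry the point: an imbalance in comorbidity fixed by eligibility, and no term in the model for it.

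**The plan's own figures.** Section 2.7 assumes d = 0.5 for anxiety versus control and states 36 per group for 80% power at two-sided 0.05. That does not reproduce: equal groups need 63 each (64 by t-test), and 36 vs 36 gives about 55% power. The step from 36 to 40 does reproduce: 36 / (1 − 0.10) = 40. With the planned 145 vs 40, power at d = 0.5 is 0.795. The mismatch is a separate matter and does not bear on this point. Only the targets of 145 and 40 are used below.

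**Illustration.** Two inputs are assumptions, because the protocol gives neither: the comorbid share p (20%, 40%, 60%) and the depression effect d_c (0.3, 0.5). The true anxiety effect is set to zero.

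- Apparent effect: d = p × d_c.
- Standard error of d near zero: √(1/145 + 1/40) = 0.179.
- Noncentrality: d / 0.179. Rejection probability from the noncentral t with 145 + 40 − 2 = 183 degrees of freedom, two-sided 0.05.

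| d_c | p | apparent d | noncentrality | rejection |
|---|---|---|---|---|
| 0.3 | 20% | 0.06 | 0.34 | 0.063 |
| 0.3 | 40% | 0.12 | 0.67 | 0.103 |
| 0.3 | 60% | 0.18 | 1.01 | 0.171 |
| 0.5 | 20% | 0.10 | 0.56 | 0.086 |
| 0.5 | 40% | 0.20 | 1.12 | 0.200 |
| 0.5 | 60% | 0.30 | 1.68 | 0.386 |

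A normal approximation that allows for the extra variance among patients from mixing comorbid and non-comorbid cases agrees to within 0.001. The figures are per index and before false discovery rate adjustment, so they are not the plan's error rates.

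**Precision of a subset without comorbid depression, at d = 0.5 against 40 controls**

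| comorbid share | patients left | standard error of d, √(1/n + 1/40) | power |
|---|---|---|---|
| none removed | 145 | 0.179 | 0.80 |
| 20% | 116 | 0.183 | 0.77 |
| 40% | 87 | 0.191 | 0.74 |
| 60% | 58 | 0.206 | 0.67 |

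The loss is modest because the 40 controls dominate the variance: 1/40 = 0.025, against 1/145 = 0.007 and 1/87 = 0.011.

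**The case against.** The strongest reply is that admitting comorbid patients is the design. The study is transdiagnostic, all analyses are declared exploratory in section 3.4, and the Introduction gives the controls the modest role of a reference for normal variation, which a never-ill group serves. This stands as a defence of eligibility. It does not settle attribution: the boundaries that the Introduction proposes to cross are those between panic disorder, social anxiety disorder, generalised anxiety disorder, agoraphobia and specific phobia. Pooling these does not license calling a depression-driven difference an anxiety difference.

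A second reply is that sensitivity analyses belong in a fuller plan and that section 3.4 includes covariates as needed. That lowers the weight of the point. However, section 3.2 does name the model and its covariates, and neither list includes comorbidity.

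Third, the primary objective hardly depends on this contrast. Response is defined and predicted within patients, and the responder versus non-responder comparison uses no controls. Section 3.3 also enters psychiatric history and psychometric scores as predictors, and a feature must still predict response under cross-validation. An index that reflects depression and predicts response is a valid predictor. All of this stands. What remains is the patient-control contrast, the three-group models in section 3.3 that use the same controls, and a possible effect on which features are considered.

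A reader might also infer that the groups differ in all other psychopathology. They do not, since psychotic illness and current substance or alcohol use disorder are barred on both sides. Nor is d = 0.5 the plan's figure for depression: section 2.7 assumes it for anxiety versus control, and its use above as a depression effect is purely illustrative.

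**Conclusion.** The point holds for the secondary patient-control contrast. As eligibility and section 3.2 are written, a difference there cannot be attributed to anxiety rather than to comorbid depressive or other disorders. A reader might go further and infer that the response-prediction models are invalid or that comorbid patients should be excluded; the documents support neither.

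The size cannot be determined from the protocol. An apparent d of 0.06 to 0.30 and a per-index rejection probability of 6% to 39% rest on assumed comorbid shares and depression effects and on an anxiety effect of exactly zero. At the lower end the distortion is close to the nominal 5%. The case for a change rests on the unsupported attribution and the small cost of addressing it.

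**What to change.** In section 3.2, add a sensitivity analysis that repeats each patient-control comparison in patients with no comorbid depressive disorder on the MINI and, where numbers allow, no other non-anxiety disorder. Report the full-sample and subset estimates together, with confidence intervals and with baseline anxiety severity in each set. Severity is needed because patients without depression may also be less anxious, so a smaller subset estimate could reflect milder anxiety rather than the removal of comorbidity.

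Describe full-sample differences as differences between patients with anxiety disorders, including their comorbidity, and never-ill controls. Call an index anxiety-related only with the subset estimate and interval shown beside it. Set no fixed retention threshold and no second significance test: with a standard error of about 0.19 in the subset, either would be a noisy rule.

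The cost is one repeat of an existing model on data already collected. Precision falls, for example from 80% to 74% power at d = 0.5 if 40% of patients are comorbid. Removing depressive disorder found on the MINI may leave past episodes and, where numbers are small, other comorbidity in place; the report should say so.

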### 2.3. Recruitment Process and Screening for Enrollment

The clinical anxiety group will be recruited through outpatient psychiatric clinics at Samsung Kangbuk Hospital, where attending psychiatrists will identify individuals who meet the inclusion criteria. The healthy control group will be recruited via public announcements on institutional bulletin boards.

To confirm eligibility and psychiatric status, all participants will be evaluated by a board-certified psychiatrist using structured diagnostic interviews. The Structured Clinical Interview for DSM-5 Disorders will be used to verify diagnoses in the clinical anxiety group [27], while the Mini International Neuropsychiatric Interview (MINI) 5.0.0 will be administered to screen for comorbid conditions or to confirm the absence of psychiatric history in healthy controls [28].

All eligible participants will receive a detailed explanation of the study’s purpose, procedures, potential risks, and their rights. Written informed consent will be obtained before any assessments are conducted. Participation is entirely voluntary, and individuals may withdraw at any time without affecting their clinical care.

### 2.4. Discontinuation and Dropout Criteria

Participants may be discontinued from the study under the following circumstances: emergence of adverse events or significant exacerbation of symptoms, voluntary withdrawal of consent, development of serious medical or psychiatric conditions that preclude continued participation, or the principal investigator’s judgment that termination is necessary for the participant’s well-being.

Dropout is defined as non-compliance with the study protocol, including missing scheduled assessments or failing to attend follow-up visits within the designated visit window (±15 days from the scheduled date).

In cases of either discontinuation or dropout, the principal investigator will inform the participant of the rationale and any necessary actions to be taken. The research team will take all reasonable steps to ensure participant safety, including offering follow-up care or appropriate referrals. With the participant’s consent, data collected prior to withdrawal may be retained and used for analysis.

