### 2.5. Observational Parameters and Clinical and Laboratory Assessments

Participants in the clinical anxiety group will complete assessments at four timepoints: baseline and 2, 6, and 12 months. The healthy control group will be assessed at baseline and 12 months. The timepoints were chosen to efficiently assess symptom improvement at 2 months, check for relapse at 12 months for the clinical anxiety group, and confirm continued health for the healthy control group. These intervals also minimize participant burden while ensuring comprehensive data collection over the course of a year. Assessments will include clinical interviews, standardized self-report questionnaires, computerized neurocognitive testing, VR-based behavioral evaluations, physiological recordings (EEG and ECG), and multimodal brain imaging (structural, functional, and diffusion MRI).

Given the 12-month follow-up period and the multimodal nature of the assessments, challenges related to participant burden and attrition are anticipated. To mitigate these risks, the study incorporates flexible scheduling, abbreviated interim assessments at selected follow-up visits, and the option for remote administration of questionnaires where appropriate. These strategies are intended to support participant retention and ensure data completeness while maintaining methodological rigor.

Figure 2 summarizes the timing and scope of these assessments across both groups. At each timepoint, specific instruments have been selected to capture transdiagnostic symptom dimensions and neurobehavioral mechanisms aligned with the RDoC framework—particularly domains related to Negative Valence Systems, Cognitive Systems, and Arousal/Regulatory Systems.

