### 3.4. Statistical Considerations

All analyses will be exploratory and hypothesis-generating. Normality of data distributions will be verified using the Shapiro–Wilk test and residual diagnostics. If assumptions for parametric tests are violated, appropriate transformations or non-parametric alternatives will be employed. Potential covariates (age, sex, medication status, treatment type) will be included as needed. Missing data will be handled using multiple imputation or complete-case analysis, depending on the extent and mechanism of missingness.

To ensure generalizability, model interpretability, and prevention of overfitting, we will report confidence intervals, cross-validation performance variability, and model calibration statistics where applicable. Robustness checks (e.g., bootstrapping with 1000 iterations) will be performed to confirm model stability. All analyses will be implemented in R (version 4.3.1 or later) and Python (version 3.10 or later). The analysis code will be managed using a version-controlled repository (Git), and the final software environment, including package versions, will be documented to ensure reproducibility.

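### One missed or late visit counts as dropout and worsening patients may be discontinued, with no provision for later PDSS scores, so obtainable outcomes may be lost

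*Protocol article*

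**What the plan says.** Section 2.4 of the protocol article gives two routes out of the study.

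- **Dropout.** "Dropout is defined as non-compliance with the study protocol, including missing scheduled assessments or failing to attend follow-up visits within the designated visit window", the window being plus or minus "15 days from the scheduled date". No minimum number of missed or late visits is stated.
- **Discontinuation.** This is permitted on several grounds, among them "emergence of adverse events or significant exacerbation of symptoms".

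The section then treats both routes together. The investigator explains the reason to the participant, and with consent "data collected prior to withdrawal may be retained and used for analysis". Nothing is said about scores obtained after either event.

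Section 2.5 sets the schedule: "Participants in the clinical anxiety group will complete assessments at four timepoints: baseline and 2, 6, and 12 months". For retention, "the study incorporates flexible scheduling, abbreviated interim assessments at selected follow-up visits, and the option for remote administration of questionnaires where appropriate". Section 2.5.2 allows questionnaires by telephone or a secure online platform.

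Section 2.6 defines response as a PDSS fall of at least 40% from baseline at each follow-up and classes everyone else as a non-responder. For analysis, Section 3.3 names multiple imputation by chained equations, or something similar, for the prediction models. Section 3.4 says more generally: "Missing data will be handled using multiple imputation or complete-case analysis, depending on the extent and mechanism of missingness".

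**The concern.** Section 2.1 says that the research protocol gives no structured treatment, so discontinuing a patient ends observation and nothing else. A missed visit in such a cohort is one missing value, and a late visit is one mistimed value. Section 2.4 puts both in the same class as leaving the study and makes no provision for using a late score or holding the later visits.

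The worsening route raises a further problem. A patient whose symptoms clearly worsen will generally not have a 40% PDSS fall at that time, and so would be a non-responder at that visit under Section 2.6. Section 2.5 gives checking for relapse as a purpose of the 12-month visit, yet a severe relapse before then is itself a ground for discontinuation.

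If such patients have no later score, complete-case analysis leaves them out and is biased. Imputation that assumes missing at random would not reliably repair this, because the reason for missingness is tied to the unseen outcome. Non-responders are the smaller class at the assumed 25%, so losses there weigh most on the prediction models.

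**Working it through.** **Inputs from the document.** Clinical group 145, dropout 20%, non-response 25% (Section 2.7). Three follow-up visits for the anxiety group (Section 2.5).

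**Assumed here, not in the document.** The ratio RR of dropout risk in non-responders to that in responders, the per-visit rate m of missed or late attendance, and independence between visits.

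**1. The plan's own figure.** Section 2.7 wants at least 80 non-responders. Its inputs give 145 × 0.80 = 116 patients with an outcome, and 116 × 0.25 = 29 non-responders. The figure of 80 is not reproduced. That is a separate problem in Section 2.7, but it makes 29 the fair baseline here: ordinary non-selective dropout already takes the 145 × 0.25 = 36.25 non-responders enrolled down to 29.

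**2. Selective loss.** Hold overall dropout at 20%. Dropout in responders is d_R = 0.20 / (0.75 + 0.25 × RR), and in non-responders d_N = RR × d_R. Non-responders with an outcome number 36.25 × (1 − d_N), out of 116.

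| RR | d_R | d_N | Non-responders with outcome | Observed non-response |
|---|---|---|---|---|
| 1 | 0.200 | 0.200 | 29.00 | 25.0% |
| 2 | 0.160 | 0.320 | 24.65 | 21.2% |
| 3 | 0.133 | 0.400 | 21.75 | 18.8% |

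RR = 3 corresponds to half of the 29 dropouts being non-responders: 36.25 − 14.5 = 21.75.

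**3. How unscored patients are classified.** At RR = 3, complete-case analysis gives 21.75/116 = 19% non-response. Counting every unscored patient as a non-responder gives (21.75 + 29)/145 = 35%. The true rate in this scenario is 25%. Section 2.6 does not settle which applies.

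**4. Strictness of the visit rule.** If one miss in three visits makes a dropout, the share is 1 − (1 − m)³:

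- m = 5%: 14.3%
- m = 10%: 27.1%
- m = 15%: 38.6%

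The planned 20% is used up at m = 1 − 0.8^(1/3) = 7.2% per visit.

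**The case against.** A reader might infer that both rules remove non-responders selectively. The document does not support that for missed or late visits. Nothing links lateness to non-response, and recovered patients may equally stop attending.

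Nor does the text say that late scores are discarded or later visits cancelled. The sentence on earlier data can be read as a consent provision, and discontinuation is optional. What stands is narrower: one miss meets the definition, and later scores are not provided for.

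A worsening patient is also not a non-responder by definition. Section 2.4 speaks of symptoms in general, whereas response rests on the PDSS in a sample that includes social anxiety, generalized anxiety and specific phobia. Response is judged at each visit, so a patient who worsens early may respond later. This limits the claim to a likely association at the time of worsening.

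Flexible scheduling can operate inside a window about a month wide, so Section 2.5 does not contradict Section 2.4. Section 3.3 already names multiple imputation for the models, Section 3.4 ties the method to the missingness mechanism, and the Discussion acknowledges attrition. Details of imputation may properly sit in an analysis plan that is not shown. None of this recovers a score that was never sought.

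The numbers are illustrative. The document gives no support for any particular risk ratio or per-visit rate, and only an unknown share of dropouts would be discontinued for worsening. Missed visits tend to cluster within patients, which lowers the share with any miss at a given per-visit rate.

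**Conclusion.** The point holds as a risk created by the wording of Section 2.4. Followed as written, the section can lose PDSS outcomes that could have been obtained. For patients discontinued because of worsening, that loss is likely to be related to outcome. For missed or late visits it is an avoidable loss of data with no demonstrated direction.

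Against a baseline of 29 non-responders, dropout at two to three times the responders' rate would cost about 4 to 7 of them (29 − 24.65 = 4.35; 29 − 21.75 = 7.25) and lower observed non-response from 25% to 21% or 19%. This rests on the plan's 25% and 20% and on assumed risk ratios. The 7.2% per-visit tolerance rests on independent visits and on every single miss being counted as dropout. Correcting the rule is a cheap improvement, and no finding of actual bias is made.

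**What to change.** In Section 2.4, define dropout as withdrawal of consent or loss of contact. Treat a missed visit as missing at that visit only, and continue with later visits. Keep out-of-window PDSS scores with their actual dates.

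Leave the safety decision on discontinuation as it is. With consent, continue to seek the PDSS and the secondary scales after discontinuation by the telephone or online route that Section 2.5.2 already allows.

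For analysis, make multiple imputation that includes the reason for missingness primary. Add two sensitivity analyses: complete cases, and coding patients discontinued for worsening as non-responders at later visits without a score. The second should not be primary, because it would mislabel patients who recover. State in Section 2.6 how a patient without a score is classified.

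The cost is a change of wording, some extra remote contacts, and more spread in visit timing.
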